# Clinical and cost-effectiveness of bracing in symptomatic knee osteoarthritis management: protocol for a multicentre, primary care, randomised, parallel-group, superiority trial

**DOI:** 10.1136/bmjopen-2020-048196

**Published:** 2021-03-26

**Keywords:** rheumatology, primary care, musculoskeletal disorders

## Abstract

**Background:**

Brace effectiveness for knee osteoarthritis (OA) remains unclear and international guidelines offer conflicting recommendations. Our trial will determine the clinical and cost-effectiveness of adding knee bracing (matched to patients’ clinical and radiographic presentation and with adherence support) to a package of advice, written information and exercise instruction delivered by physiotherapists.

**Methods and analysis:**

A multicentre, pragmatic, two-parallel group, single-blind, superiority, randomised controlled trial with internal pilot and nested qualitative study. 434 eligible participants with symptomatic knee OA identified from general practice, physiotherapy referrals and self-referral will be randomised 1:1 to advice, written information and exercise instruction and knee brace versus advice, written information and exercise instruction alone. The primary analysis will be intention-to-treat comparing treatment arms on the primary outcome (Knee Osteoarthritis Outcomes Score (KOOS)-5) (composite knee score) at the primary endpoint (6 months) adjusted for prespecified covariates. Secondary analysis of KOOS subscales (pain, other symptoms, activities of daily living, function in sport and recreation, knee-related quality of life), self-reported pain, instability (buckling), treatment response, physical activity, social participation, self-efficacy and treatment acceptability will occur at 3, 6, and 12 months postrandomisation. Analysis of covariance and logistic regression will model continuous and dichotomous outcomes, respectively. Treatment effect estimates will be presented as mean differences or ORs with 95% CIs. Economic evaluation will estimate cost-effectiveness. Semistructured interviews to explore acceptability and experiences of trial interventions will be conducted with participants and physiotherapists delivering interventions.

**Ethics and dissemination:**

North West Preston Research Ethics Committee, the Health Research Authority and Health and Care Research in Wales approved the study (REC Reference: 19/NW/0183; IRAS Reference: 247370). This protocol has been coproduced with stakeholders including patients and public. Findings will be disseminated to patients and a range of stakeholders.

**Trial registration number:**

ISRCTN28555470.

Strengths and limitations of this studyLarge, publicly funded trial addressing an important unresolved question around affordable, effective non-pharmacological management of painful knee osteoarthritis.Recruitment from a broad range of settings (general practice, physiotherapy services and self-referral following awareness raising).The intervention arm of our pragmatic design stratifies the provision of brace type based on predominant clinical and radiographic features at presentation, incorporates adherence support components and is delivered by physiotherapists—a scalable model for future implementation.Restricted range of off-the-shelf brace options included.The trial is powered for the overall comparison between treatment arms but not for subgroup analyses of different brace types.

## Introduction

Symptomatic knee osteoarthritis (OA) affects an estimated 10% of adults aged over 55 years^1^ and has a significant impact on population health, healthcare demand and societal costs. Trends in disability-adjusted life-years attributed to OA,^2^ the number and rate of primary knee replacements,^3–6^ and rates of new presentations to primary care^7^ all suggest an increasingly common problem that accounts for up to 0.5% gross domestic product in high-income countries.^8 9^

In the UK, the National Institute for Health and Care Excellence (NICE) currently recommends that people with OA who have ‘biomechanical joint pain with or without instability should be considered for assessment for bracing as an adjunct to their core treatments’.^10^ However, there remains a lack of high-quality trials on their clinical and cost-effectiveness. While some international clinical guidance recommend bracing for knee OA,^11 12^ several others have been unable to make a recommendation due to the limited evidence base.^13–16^

A Cochrane review, originally published in 2005^17^ and updated in 2015,^18^ identified five randomised controlled trials (RCTs),^19–23^ with sample sizes ranging from 33 to 117, that compared a type of brace for OA of the knee versus no treatment or other treatment such as restricted activity, patient education, exercise, pharmacological treatment and orthoses or surgical treatment. The review concluded that ‘low-quality evidence suggests that people with OA who use a knee brace may have little or no reduction in pain or improvements in knee function and quality of life’. Since then, five further systematic reviews^16 24–27^ and one narrative review^28^ have been published and identified a total of 13 RCTs,^29–41^ (two RCTs were published after the Cochrane review).^40 41^ These concluded that either the existing evidence is insufficient,^16 26 27^ or is consistent with small-to-moderate effects on pain and function for unloader braces^24^ and soft sleeve braces^25^; therefore, further investigation is warranted. Only three trials^20 21 29^ and one observational study^42^ followed participants up for 6 months or longer.

The current trial was designed in response to a commissioned call from the National Institute for Health Research Health Technology Assessment programme for an efficient and pragmatic trial to investigate, in primary care, the clinical and cost-effectiveness of knee braces in the management of knee OA.

## Objectives

The overall aim of the ‘PROvision of braces for Patients with knee OA’ (PROP OA) trial is to determine the clinical and cost-effectiveness of adding knee bracing (matched to patients’ clinical and radiographic presentation and with adherence support) to advice, written information and exercise instruction compared with advice, written information and exercise instruction alone, in adults with symptomatic knee OA.

Specifically, our primary objective is to determine, in adults with symptomatic knee OA, if the advice, written information and exercise instruction plus knee brace is superior to advice, written information and exercise instruction alone for Knee Osteoarthritis Outcomes Score (KOOS)-5, a composite score of patient-reported pain, other symptoms, activities of daily living (ADLs), function in sport and recreation and knee-related quality of life, at 6 months.

Key secondary objectives are to determine, in adults with symptomatic knee OA:

If the advice, written information and exercise instruction plus knee brace is superior to advice, written information and exercise instruction alone for KOOS-5 at 3 and 12 months.If the advice, written information and exercise instruction plus knee brace is superior to advice, written information and exercise instruction alone for the separate components of KOOS-5 (patient-reported pain, other symptoms, ADLs, function in sport and recreation and knee-related quality of life) at 3, 6 and 12 months.Cost-effectiveness of the advice, written information and exercise instruction plus knee brace compared with advice, written information and exercise instruction alone.

Other secondary objectives are to determine:

If the advice, written information and exercise instruction plus knee brace is superior to advice, written information and exercise instruction alone for: self-reported pain; instability (buckling); treatment response; physical activity; social participation; arthritis self-efficacy.Safety of knee bracing in adults with symptomatic knee OA ((serious)- related adverse events (SAE)).Acceptability and experiences of the trial procedures and interventions to participants receiving and physiotherapists delivering, the trial interventions.Adherence to interventions, including exploring barriers and enablers of adherence to brace use in participants allocated to the advice, written information and exercise instruction plus knee brace intervention.

A priori exploratory subgroup analyses will explore the effectiveness of the knee brace plus advice, written information and exercise instruction intervention versus advice, written information and exercise instruction alone by: (1) predominant knee compartmental involvement, (2) knee buckling, (3) adherence to brace use, (4) anxiety/depression. We will also explore how often physiotherapists’ clinical judgement on appropriate brace type is changed by plain X-ray findings.

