### Cointerventions

All participants will be advised that they can continue to access usual healthcare, including medications and consultations with other health professionals. Participants allocated to the comparator arm will be asked not to wear a knee brace for the 6-month period following randomisation. Details of cointerventions will be recorded in follow-up questionnaires.

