#### Adherence

Adherence to interventions will be measured via self-report in follow-up questionnaires (using similar questions to those we have used in previous trials of non-pharmacological care for OA).^44^ In those randomised to advice, written information and exercise instruction plus knee brace, SMS text messages will also seek data on number of days per week and hours per day of brace usage, sent on a tapering schedule over the first 6 months of follow-up, with a text message also at 12 months. We will seek to include an objective measure of adherence to brace use, with participants blinded to this.

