Exploratory subgroup analyses will be performed (if numbers in each subgroup are sufficient for these analyses to be feasible) based on the presence of knee instability (buckling), predominant knee compartment involved, level of adherence and anxiety/depression. Participants will also be included in a per-protocol analysis if they meet prespecified inclusion criteria, defined fully in the a priori analysis plan. Cross-tabulation and the kappa statistic will be used to test how accurate brace allocation would have been if based on clinical judgement alone, rather than on clinical assessment findings and X-ray assessment combined. Treatment acceptability will be described using numbers and percentages. Any adverse events and protocol violations will be reported throughout the trial by intervention arm. No interim analysis will be undertaken during the trial to assess the clinical effectiveness of advice, written information and exercise instruction plus knee bracing over advice, written information and exercise instruction alone, however, an internal pilot trial phase will be conducted with prespecified progression criteria (online supplemental datafile 1).

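### Adherence to brace use is listed as a subgroup factor, but it arises after randomisation and only in the brace arm, so it cannot give a randomised subgroup effect

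*Protocol article*

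**What the plan says.** The Objectives set out the contrast and the factors together. The contrast is between arms: "A priori exploratory subgroup analyses will explore the effectiveness of the knee brace plus advice, written information and exercise instruction intervention versus advice" and written information and exercise alone. The factors are "1) predominant knee compartmental involvement, (2) knee buckling, (3) adherence to brace use, (4) anxiety/depression". The Statistical methods repeat the commitment, with the analyses "based on the presence of knee instability (buckling), predominant knee compartment involved, level of adherence and anxiety/depression". Neither place separates adherence from the other three.

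Other sections show what kind of variable each factor is:

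- **Allocation:** compartment and buckling are randomisation strata.
- **Table 2:** the anxiety and depression scales are completed at enrolment only. Adherence is recorded only after randomisation, by text message from week 1 to week 52 and by questionnaire at 3, 6 and 12 months.
- **Cointerventions:** "Participants allocated to the comparator arm will be asked not to wear a knee brace for the 6-month period following randomisation".
- **Adherence:** for participants randomised to the brace, "SMS text messages will also seek data on number of days per week and hours per day of brace usage". Questionnaires also ask about adherence to the interventions in general, without limiting this to one arm.
- **Follow-up treatment session:** brace use is stepped up in those who tolerate the brace and find it helpful, and may be cut back in those who do not.

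**The concern.** A subgroup effect compares the arms within each level of a factor, so both arms must have members at each level and randomisation must not have influenced membership. Brace adherence fails both conditions. What remains is to compare part of the brace arm, chosen by behaviour after randomisation, with some or all of the comparator arm.

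That comparison mixes any brace effect with the reasons people keep wearing a brace: better prognosis, better general engagement, and having already felt benefit. Adherence support is part of the intervention named in the trial's overall aim, so a finding that the brace works if worn is one that readers will look for. Listed as an a priori subgroup result, it would carry more authority than the design can give it.

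**Working it through.** **1. The plan's own figure.** The sample-size paragraph (after Figure 1) gives an effect size of 0.35, two-sided 5%, 90% power, SD 23, MCID 8, 173 per arm analysed and 434 randomised with 20% loss.

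- Normal approximation: 2 × (1.960 + 1.282)² / 0.35² = 171.6, so 172 per arm. The t-test version gives 172.5, so 173.
- 0.35 × 23 = 8.05 points, which agrees with the MCID of 8.
- 346 / 0.8 = 432.5, and 434 covers this.

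The sample size reproduces, and this point does not affect it. SD 23 and 173 per arm are carried forward.

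**2. Factors side by side.**

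| Factor | When measured | Value in both arms? |
|---|---|---|
| Compartment | before randomisation (stratum) | yes |
| Buckling | before randomisation (stratum) | yes |
| Anxiety/depression | enrolment only | yes |
| Adherence to brace use | after randomisation only | no |

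The only brace-use bands in the document are the low, mid and high bands for tailoring text messages (Motivational prompts). By those bands, a comparator who follows the request not to wear a brace is always low. The mid and high cells have no comparators, so the interaction has nothing to estimate it from.

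**3. Size of the possible bias, with a true brace effect of zero.** Two inputs are assumptions and are not in the documents:

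- p, the share of the brace arm called adherent;
- ρ, the correlation between the tendency to adhere and 6-month KOOS-5 that remains after covariate adjustment.

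If the top share p on a normal adherence tendency is called adherent, with c = z(1 − p) and φ the normal density:

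- adherers minus all comparators = ρ × SD × φ(c) / p
- non-adherers minus all comparators = −ρ × SD × φ(c) / (1 − p)

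For p = 0.5, c = 0 and φ(0) / 0.5 = 0.3989 / 0.5 = 0.798, so the bias is ρ × 23 × 0.798 = 18.35ρ.

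| ρ | Adherers vs comparators | Non-adherers vs comparators | False gap | Chance of p < 0.05 for adherers |
|---|---|---|---|---|
| 0.1 | +1.8 | −1.8 | 3.7 | 9% |
| 0.2 | +3.7 | −3.7 | 7.3 | 23% |
| 0.3 | +5.5 | −5.5 | 11.0 | 46% |

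The last column compares 173 × 0.5 = 86.5 adherers with 173 comparators. At ρ = 0.2 the standard error is √(515.5/86.5 + 529/173) = 3.00, so the shift is 3.67 / 3.00 = 1.22 standard errors and the two-sided rejection rate is 23% rather than 5%.

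Over p = 0.3 to 0.7 and ρ = 0.1 to 0.4, the adherer contrast runs from +1.1 to +10.7 points and the rejection rate from 7% to 87%.

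The bias is proportional to the SD. If adjustment for baseline covariates leaves a residual SD below 23, these figures shrink in proportion at the same residual ρ.

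**The case against.** **The article fixes no estimator.** It prescribes neither an interaction test nor adherers against all comparators, calls its statistics section a brief outline, and defers to a separate plan. This is true. What it does fix, in two places, is that brace adherence is a subgroup factor for the between-arm effect. No choice of model makes that a subgroup effect in the sense that holds for the other three factors, and an analysis plan would inherit the wording.

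**The analyses are exploratory and conditional.** The text says "Exploratory subgroup analyses will be performed (if numbers in each subgroup are sufficient for these analyses to be feasible". This limits the claims that can be made and the severity of the point. It does not remove bias, and larger numbers only make a biased contrast more likely to reach significance.

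**The Statistical methods say only level of adherence.** That could be read as adherence to exercise, which the questionnaires might capture in both arms. The Objectives specify brace use, however, and exercise adherence would still be a post-randomisation variable.

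**A stronger reading that does not hold: the per-protocol analysis.** A reader might infer that it has the same defect, dropping poor adherers from the brace arm and almost nobody from the comparator arm. The document does not say so: "Participants will also be included in a per-protocol analysis if they meet prespecified inclusion criteria, defined fully in the a priori analysis plan". No criterion is stated. The criteria may well cover both arms, since brace wear by a comparator is a possible deviation. That per-protocol sets are open to selection is a general caution, not an error shown here.

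**A further overstatement.** It goes slightly too far to say that comparators cannot have any brace use. One could wear a brace against the request, but that would be contamination, not adherence to an allocated treatment.

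**Conclusion.** The point holds for the adherence subgroup. The protocol article twice lists a post-randomisation variable, specific to one arm and partly driven by response, among baseline subgroup factors for a between-arm effect. This is a fault in what the text commits to, not a detail left to the analysis plan.

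The illustrative size is 1.8 to 5.5 KOOS-5 points of spurious benefit among adherers, against an MCID of 8. It rests on SD 23 from the document, an assumed 50% adherence and an assumed residual correlation of 0.1 to 0.3. It shows what modest selection could produce and does not measure bias in this trial.

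Severity is moderate. A reader might infer that the trial's main conclusion is at risk, but the documents do not support that: the primary analysis is intention-to-treat, the sample size reproduces, and the affected analysis is exploratory.

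**What to change.** 1. Delete adherence from the subgroup lists in the Objectives and the Statistical methods, leaving compartment, buckling and anxiety/depression.
2. Report associations between brace use and outcome within the brace arm only, descriptively and labelled as non-randomised.
3. If a causal adherence question is wanted, prespecify a complier-average causal effect on KOOS-5 at 6 months as a secondary exploratory analysis, with randomised arm as the instrument and an adherence threshold fixed before the data are seen.

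Item 3 is optional, and its main assumption needs to be stated openly. The exclusion restriction says that allocation affects outcome only through adherence as defined. That is strained here: the brace arm has a 1-hour session and a 30-minute follow-up visit against a single 20-minute consultation, plus motivational techniques, a diary and text messages. A yes/no threshold also counts partial wearers as untreated. If the extra contact alone were worth an assumed 2 points to everyone, with no brace effect and 50% adherence, the estimate would be 2 / 0.5 = 4 points, all of it wrongly credited to the brace. A sensitivity analysis over a range of such direct effects should therefore accompany it.

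The cost is a change of wording in two places and, if item 3 is adopted, one two-stage model with its sensitivity analysis on brace-use data already being collected. The downside of item 3 is a wider interval and an assumption that cannot be tested.

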## Design

A multi-centre, primary care, randomised (1:1), parallel-group, superiority trial with internal pilot (see online supplemental datafile 1 for further details relating to the internal pilot and progression criteria). The trial protocol has been coproduced with stakeholders including patients.

10.1136/bmjopen-2020-048196.supp1Supplementary data

### Setting

Participants will be recruited from National Health Service (NHS) general practice, physiotherapy services and from self-referral within the community following an awareness raising campaign. Interventions will be delivered within PROP OA knee pain clinics based in physiotherapy services at four NHS sites with onsite radiography departments in England (Cheshire, Manchester, Northumbria and Staffordshire).

### Eligibility criteria

The target population is adults aged ≥45 years with symptomatic knee OA, moderate-to-severe pain during weight-bearing activity, with or without knee buckling, who have no current or recent knee brace use but who would be willing to consider using a knee brace (table 1).

**Table 1 T1:** Eligibility criteria

Inclusion criteria	Exclusion criteria
Aged 45 years and over Residing in England Clinically significant knee pain on weight bearing (NRS ≥4) With or without knee instability (buckling) Able to have knee X-ray Able to read and write English Access to a mobile phone that can receive SMS text messages Able to give full informed consent Willing to participate	Red flags in the history or clinical examination that may indicate further investigation or referral for possible serious underlying pathology (NICE V.5.1.1.^10^) Vulnerable individuals (eg, in palliative phase of care for cancer, unstable mental health disorders). Inflammatory/crystal arthritis (eg, rheumatoid arthritis, gout, psoriatic arthritis). Significant neurological disorder (eg, stroke, Parkinson’s disease, multiple sclerosis, dementia). Fibromyalgia. Symptoms not attributable to knee OA. Previous major surgery in the knee to be treated (partial/total knee replacement; high tibial osteotomy, not other previous arthroscopic surgery). Autologous cartilage implantation in last 12 months in the knee to be treated On the waiting list for total hip or knee replacement within the next 6 months. Unwilling to wear a knee brace. Brace size unavailable for leg circumference. Knee brace contraindicated (superficial wounds where the knee brace would reside, psoriasis, eczema or poor circulation, arterial insufficiency, or severe varicosities that could result in skin at risk with regular brace wear, a history of thrombophlebitis in either leg). Significant fixed flexion deformity that prevents fitting of brace. Injection in the knee to be treated within the last 3 months. Recent/routine knee brace wear within the last 3 months. Nursing home resident. Unable to attend clinic. Close family member already a trial participant. Course of physiotherapy for the knee to be treated in the last 3 months.

NICE, National Institute for Health and Care Excellence; NRS, Numerical Rating Scale; OA, osteoarthritis.

### Participant identification

Three methods will be used to identify potential participants, informed by our previous pragmatic trials of treatments for musculoskeletal pain conditions in primary care^43–45^:

